**Vaccination visit 2: Penta^c,d^ dose 2; OPV^e^ dose 2; PCV^f^ dose 2**			
	**30 days after vaccination visit 1 (Penta1, OPV1, and PCV1)**		
		2 days before scheduled visit	“[CaregiverName], please bring your child for immunisation this week. Confirm the date in your child health card.”
		On the day of the scheduled visit	“[CaregiverName], don’t forget to immunise your child this week. Confirm the date in your child health card.”
		2 days after the scheduled visit	“[CaregiverName], don’t forget to immunise your child this week. Confirm the date in your child health card.”
**Vaccination visit 3: Penta3, OPV3, PCV3**			
	**61 days after vaccination visit 1 (Penta1, OPV1, and PCV1)**		
		On the day of the scheduled visit	“[CaregiverName], please bring your child for immunisation. Confirm the date in your child health card.”
		5 days after the scheduled visit	“[CaregiverName], please bring your child for immunisation. Confirm the date in your child health card.”
		7 days after the scheduled visit	“[CaregiverName], please bring your child for immunisation. Confirm the date in your child health card.”
**Vaccination visit 4: measles-containing vaccine**			
	**274 days after the child’s date of birth**		
		On the day of the scheduled visit	“[CaregiverName], please bring your child for measles immunisation this week. Confirm the date in your child health card.”
		5 days after the scheduled visit	“[CaregiverName], don’t forget to immunise your child against measles. Confirm the date in your child’s health card.”
		7 days after the scheduled visit	“[CaregiverName], don’t forget to immunise your child against measles. Confirm the date in your child’s health card”

^a^Vaccination visits subsequent to the Penta1 visit were scheduled in the District Health Information System 2 Tracker at the time of registration. As such, vaccination visit 3 (Penta3, OPV3, and PCV3) was scheduled based on the date of vaccination visit 1 (Penta1, OPV1, and PCV1).

^b^Messages were sent in both English and Lugbara.

^c^Penta: pentavalent vaccine.

^d^Penta contains diphtheria, tetanus, pertussis, hepatitis B, and *Haemophilus influenzae* type b antigens.

^e^OPV: oral polio vaccine.

^f^PCV: pneumococcal conjugate vaccine.

### Data Collection

Data were collected using a variety of tools: pre- and postintervention questionnaires, immunization data extraction form, and health facility record review form. At the time of enrollment, study personnel administered the preintervention questionnaire to participants (at the Penta1 visit) to gather basic demographic and locating information. At the time of the MCV visit, study personnel administered the postintervention questionnaire to participants to gather information on the acceptability of the text message reminder intervention, knowledge, attitudes, and beliefs regarding vaccination practices, and demographic information. Participants who did not return for MCV were interviewed at their homes. In some cases, the study personnel met the participants in another location that was convenient to them and reimbursed them for their transportation costs. In some other cases, the study personnel interviewed participants by phone because it was not feasible to interview in person. As part of the postintervention questionnaire, study personnel reviewed the HBRs of the child participants to extract vaccination data.

Every day during the enrollment period, study personnel completed the health facility immunization system record review form to capture service delivery process indicators (eg, vaccination sessions held, antigens administered). In addition, study personnel extracted vaccination data on the child participants from the immunization register.

### Data Management and Analysis

Initially, data collectors completed the participant interviews on paper and then entered the data into a REDCap electronic capture tool [23] on a tablet. After becoming comfortable with the tablet, data collectors entered the data directly into the tablet. Data were stored on a cloud-based server that used a 256-bit encryption. The server backed up the data daily and was only accessible through a secure password-protected website, which had individual log-ins only for authorized users. Data were removed from the server once the project was completed.

Data quality control was addressed at multiple stages. The first stage of quality control was the data collectors themselves. Adequate training minimized the risk of procedural errors. Furthermore, questionnaires were formatted electronically, which limited the amount of missing data, as logic patterns required the study personnel to enter all required fields. The electronic tools required the data collector to input values for each field. The second level of control was the local study coordinator. During data collection, the study coordinator ensured proper sampling and interviewing through daily periodic spot checks during data gathering. The study coordinator reviewed the data entered by the data collectors and then locked each record, after which it was no longer modifiable by the data collectors. The third level of control was the principal investigator who reviewed the data to ensure that (1) the sample size was reached, (2) the eligibility requirements of each participant were met, and (3) blanks or partially completed forms were minimized.

For the primary objective, a logistic regression model with fixed effects at the health facility level will be used to analyze differences between intervention and control groups in Penta3 and MCV coverage at 12 months of age. For the assessment of timeliness, a logistic regression model with fixed effects at the health facility level will be used to analyze differences between intervention and control groups in Penta3 coverage 12 weeks after receiving Penta1 and MCV coverage at 10 months of age. In addition, Cox proportional hazards models with fixed effects at the health facility level will be used to analyze time-to-event (ie, timeliness) outcome data. The primary analyses will be based on intention-to-treat, but per-protocol analysis will also be conducted. Dates of vaccination from HBRs will be used for analysis, supplemented with dates from the immunization register extraction if HBR dates are unavailable. In addition to logistic regression, log-binomial regression models will be used to estimate risk ratios. Data will be analyzed using statistical software such as STATA, SAS, or R.

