Caregiver participant inclusion criteria were as follows: had access to a personal or household mobile phone that could receive text messages; caregiver for a child between 6 weeks and 6 months of age at the time of Penta1 vaccination visit; lived in Arua district; and was 14 years of age or older.

Caregiver participant exclusion criteria were as follows: did not have access to a mobile phone number at the time of enrollment; did not agree or was unable to consent to participate in the study; did not anticipate being the caregiver through the child’s first birthday; planned to move out of Arua district in the upcoming year; prior enrollment of the caregiver with a different child.

Illiterate caregivers who were interested in participating, gave informed consent, and met the other inclusion criteria were enrolled. The understanding was that illiterate participants would have family members or friends read the text messages to them.

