### Enrollment, Randomization, and Blinding

Study personnel were stationed in the 4 selected health facilities and recruited caregivers of children between 6 weeks and 6 months of age who presented for their Penta1 vaccinations. Study personnel explained the study, obtained consent, and enrolled the eligible caregivers who agreed to participate in the study. Study participants responded to a brief preintervention questionnaire to collect basic demographic information and locating information. The health facility staff vaccinated the children, filled out the health facility immunization register, and filled out the children’s HBRs per standard practice in Uganda [22]. For each study participant, the study personnel sent a text message to a designated short code number with information that included the caregiver’s preferred first or last name, caregiver’s mobile phone number, child’s date of birth, and the participant study ID in the following format: “Penta [ChildDOB] CN.[CaregiverName].PN.[PhoneNumber].ID. [StudyID]” (Figure 2).

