**Figure 2 figure2:**
[figure not shown]
Screenshot of mobile phone displaying data registration format used at health facility study sites in Arua, Uganda.

The information in the text message populated a centralized immunization registry database in a District Health Information System 2 (DHIS2) Software (version 2.26) Tracker Module instance created for this study. In addition, the mobile phone number of the study personnel who registered the study participant and the date that the registration text message was sent (which also served as the date of Penta1 vaccination) were recorded in the database. At the end of each day, study participants who were registered that day were randomized by computer using stratified permuted block randomization to either the control or the intervention arm, which was then recorded in the database as well. For randomization assignment, study participants were matched in order of registration to a sequence generated by nonfield study personnel before the start of enrollment. Stratification and blocking occurred at the health facility level; blocks of random size were used (lengths=2, 4, and 6) to minimize the ability to predict the next assignment. The health worker, study personnel, and participants were blinded to the randomization at assignment. However, unblinding of the intervention group occurred when they received the first text message reminder. The control group became unblinded, as they realized that they were not receiving text message reminders. On occasion, study participants shared their intervention status with health workers and field-level study personnel, thus unblinding them to the status of some caregivers. Nonfield staff study personnel who managed the database had access to intervention status after randomization assignment.

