### Sample Size

On the basis of administrative data from 2013 to 2014, we assumed a 16% Penta1-MCV dropout rate for the nonintervention group and calculated a sample size with a power of 90% and confidence level of 95% with the ability to detect a 5% decrease in dropout rate in the intervention group compared with the control group. A one-sided test was used for the sample size calculations.

Anticipated coverage of the control group was as follows: Penta1: 100% (Penta1 is an eligibility requirement); MCV: 84% (16% dropout).

Anticipated coverage of the intervention group was as follows: Penta1: 100% (Penta1 is an eligibility requirement); MCV: 89%.

We calculated the sample size based on the following formulas [24]:

and

where *n’* is the sample size of each group if we ignore the continuity correction; *n* is the sample size of each group, accounting for the continuity correction; *P_1_* is the proportion found in the first sample (0.84); *P_2_* is the proportion found in the second sample (0.89); *Q_1_* is 1 minus *P_1_* (0.16); *Q_2_* is 1 minus *P_2_* (0.11); 

 is the average of *P_1_* and *P_2_* (0.865); 

 is the average of *Q_1_* and *Q_2_* (0.135); *z_α_ is* the z-score for a one-sided test with a level of significance of .05 (1.645); *z_β_ is* the z-score for power of 90% or *z_0.10_* (1.28).

To detect a change in MCV coverage, the sample size per arm (without attrition) needed was 838. Of these 838 per arm, we anticipated a 10% loss to follow-up for caregivers who do not return to the same health facility for MCV and who cannot be found at the end of the study or who have lost their HBRs. In addition, for the purposes of quality control, approximately 100 participants (about 5%) were recruited and contacted by mobile phone after their scheduled visits to assess the reliability of the intervention at sending text messages and having those messages received by the intended individual. Thus, an adjusted sample size of 1962 participants was necessary for enrollment.

Among caregivers approached during their children’s vaccination visit 1 (Penta1, OPV1, and PCV1), we anticipated an eligibility rate of 75% and a study refusal rate of 10%, thus estimating that study personnel would need to screen 2907 caregivers in order reach the sample size.

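### The facility-only primary model is valid, but it leaves out child age at Penta1, a complete baseline covariate that could add a little power (minor)

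*Protocol article*

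**What the plan says.** Under Data Management and Analysis, the protocol article states for the primary outcomes (Penta3 and MCV coverage at 12 months of age) that "a logistic regression model with fixed effects at the health facility level will be used". The timeliness logistic models and the Cox models carry the same facility effects. In addition, "log-binomial regression models will be used to estimate risk ratios". No covariate other than facility is named.

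Under Enrollment, Randomization, and Blinding, "Stratification and blocking occurred at the health facility level". The adjustment set is therefore exactly the one stratification factor.

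The caregiver inclusion criteria (Setting and Participants) require a "caregiver for a child between 6 weeks and 6 months of age at the time of Penta1 vaccination visit". Table 1 gives 6 weeks as the scheduled age for that dose. The registration message carried the child's "date of birth, and the participant study ID in the following format", and the date of the message was stored, "which also served as the date of Penta1 vaccination". Randomisation took place at the end of the same day.

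**The concern.** Age at Penta1 is the difference between two dates held for every registered child, and it is settled before allocation. A child who starts the series well after 6 weeks has already been late once. Lateness at the first dose may carry over to later doses, and it leaves less time to complete Penta3 before the first birthday. Adjusting a randomised comparison for a baseline variable that predicts the outcome usually raises power, and here it needs no new data. The published model leaves that gain unused. The stake is a small amount of power; the validity of the test is not in question.

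**Working it through.** **Inputs from the article (Sample Size).** Control MCV coverage 0.84; intervention 0.89; power 90%; "the z-score for a one-sided test with a level of significance of .05 (1.645"); 838 per arm before attrition; 10% loss to follow-up; about 100 quality-control participants; total 1962. Allocation is taken as 1:1, from two equal arms and even block lengths.

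**Input not in the article.** The prognostic strength of age at Penta1. Assumed odds ratios (OR) per SD of age: 1.0, 0.8, 0.67 and 0.5. These correspond to about 0%, 0.9%, 3.3% and 10% of outcome variance.

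**Step 1: reproduce the stated sample size.**

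n' = [1.645·√(2·0.865·0.135) + 1.28·√(0.84·0.16 + 0.89·0.11)]² / 0.05² = 797.4

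n = (n'/4)·[1 + √(1 + 4/(n'·0.05))]² = 836.9

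With unrounded normal quantiles these become 799 and 838, so the stated 838 is reproduced. The total is 2·838/0.90 + 100 = 1962.2, which also agrees. The calculation assumes no gain from covariates.

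**Step 2: approximate gain.** Treat adjustment as raising the effective sample size to 838/(1 − R²). One-sided power, without continuity correction, is 91.2% at R² = 0, 91.4% at 1%, 91.9% at 3%, 92.4% at 5% and 93.5% at 10%. On a scale where adjustment does reduce the standard error, the reduction is 1 − √(1 − R²): 0.5% at R² = 1%, 1.5% at 3% and 5.1% at 10%.

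**Step 3: simulation of the planned model.** Logistic regression with facility effects, 838 per arm, marginal coverage held at 84% and 89%, 1500 runs per scenario. Age at Penta1 was assumed right-skewed between 6 and 26 weeks.

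| OR per SD of age | Power, facility only | Power, facility + age | SE of log OR, facility only | SE, facility + age |
|---|---|---|---|---|
| 1.0 | 89.9% | 89.8% | 0.1459 | 0.1460 |
| 0.8 | 91.9% | 92.1% | 0.1460 | 0.1467 |
| 0.67 | 92.1% | 92.8% | 0.1457 | 0.1482 |
| 0.5 | 90.5% | 93.5% | 0.1459 | 0.1541 |

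The Monte Carlo standard error of each power is about √(0.91·0.09/1500) = 0.7 points, so differences down the facility-only column are mostly noise. The comparison to read is across each row, where both models were fitted to the same simulated data. The standard error rises with adjustment, but the estimate moves away from zero by more (at OR 0.5, from 0.434 to 0.482), and so power rises.

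**Step 4: chance imbalance.** The standardised difference in mean age between arms has SD √(2/838) = 0.049. A 2-SD imbalance with OR 0.67 per SD shifts the log odds ratio by 2·0.049·|ln 0.67| = 0.04. The planned effect is ln(0.89/0.11) − ln(0.84/0.16) = 0.43, with a standard error of about 0.146.

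**Step 5: time left to complete (Texting Reminder Intervention).** The Penta3 visit is scheduled 61 days after Penta1. A child starting at 6 weeks (day 42) reaches it at day 103; one starting at 6 months (about day 183) reaches it at about day 244. That leaves about 262 and 121 days to day 365. The MCV visit is scheduled 274 days after birth, which leaves 91 days for every child whatever the age at Penta1.

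**The case against.** The strongest reply is that nothing here is wrong. The model adjusts for the only stratification factor, its test is valid, and further covariates may be named in an analysis plan that is not shown. That stands, and it is why the point is offered as an improvement to a stated model and not as an error or an omission.

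Three stronger readings are tempting, and the documents do not support them.

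- A reader might infer that adjustment gives precision at no cost. For a logistic coefficient this is false: the standard error rises and the odds ratio becomes conditional on age. What improves is power; precision improves only on a standardised risk scale.
- A reader might infer that age at Penta1 is the best predictor available. The article reports no association between age and coverage and ranks no predictors; other demographic data were also collected at baseline.
- A reader might infer that late starters have less time to be counted as covered for MCV, the outcome that sets the sample size. They do not, because that visit is scheduled from birth. The time argument applies to Penta3 at 12 months only, and even there the latest starters keep about four months.

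Protection against chance imbalance is also worth little at this sample size (step 4). Adjustment might make assumptions about missing outcomes more credible if late starters are harder to trace, but the article gives nothing from which to size that benefit.

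Finally, a log-binomial model with continuous age may fail to converge at coverage of 84% to 89%. A change of model made after data cleaning, when database staff could see allocation, could also look data-driven. Both objections stand, and the fix allows for them.

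**Conclusion.** Minor. The facility-only model is sound and consistent with the design. Adding age at Penta1 would change one-sided power at 838 per arm by about 0 to 1 point if age is a null to moderate predictor, and by about 3 points if it is strong (OR 0.5 per SD, about 10% of outcome variance). If age is not prognostic there is essentially no loss. These figures rest on assumed prognostic strengths, an assumed age distribution, the planned 84% and 89% coverage, and the one-sided 0.05 level of the sample size calculation. The link between age and completion is plausible, but the document does not demonstrate it.

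**What to change.** Before any comparison of outcomes by arm:

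- Specify the primary logistic model and the Cox models as arm + facility + age at Penta1 (continuous).
- Obtain the risk ratio, and a risk difference, by standardisation from the logistic model. The reported effect then stays marginal, and non-convergence of a log-binomial model is avoided.
- Keep the facility-only model as a sensitivity analysis.
- Record the date of the change and that it was made blind to outcome by arm.

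The cost is one extra covariate, a standardisation step and a dated note, with no new data. The adjusted odds ratio will be conditional on age and have a slightly larger standard error, which the report should state.

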### Sample Size

On the basis of administrative data from 2013 to 2014, we assumed a 16% Penta1-MCV dropout rate for the nonintervention group and calculated a sample size with a power of 90% and confidence level of 95% with the ability to detect a 5% decrease in dropout rate in the intervention group compared with the control group. A one-sided test was used for the sample size calculations.

Anticipated coverage of the control group was as follows: Penta1: 100% (Penta1 is an eligibility requirement); MCV: 84% (16% dropout).

Anticipated coverage of the intervention group was as follows: Penta1: 100% (Penta1 is an eligibility requirement); MCV: 89%.

We calculated the sample size based on the following formulas [24]:

and

where *n’* is the sample size of each group if we ignore the continuity correction; *n* is the sample size of each group, accounting for the continuity correction; *P_1_* is the proportion found in the first sample (0.84); *P_2_* is the proportion found in the second sample (0.89); *Q_1_* is 1 minus *P_1_* (0.16); *Q_2_* is 1 minus *P_2_* (0.11); 

 is the average of *P_1_* and *P_2_* (0.865); 

 is the average of *Q_1_* and *Q_2_* (0.135); *z_α_ is* the z-score for a one-sided test with a level of significance of .05 (1.645); *z_β_ is* the z-score for power of 90% or *z_0.10_* (1.28).

To detect a change in MCV coverage, the sample size per arm (without attrition) needed was 838. Of these 838 per arm, we anticipated a 10% loss to follow-up for caregivers who do not return to the same health facility for MCV and who cannot be found at the end of the study or who have lost their HBRs. In addition, for the purposes of quality control, approximately 100 participants (about 5%) were recruited and contacted by mobile phone after their scheduled visits to assess the reliability of the intervention at sending text messages and having those messages received by the intended individual. Thus, an adjusted sample size of 1962 participants was necessary for enrollment.

Among caregivers approached during their children’s vaccination visit 1 (Penta1, OPV1, and PCV1), we anticipated an eligibility rate of 75% and a study refusal rate of 10%, thus estimating that study personnel would need to screen 2907 caregivers in order reach the sample size.

According to administrative data from the operational year 2013 to 2014, the 3 largest health facilities in and around Arua town administered a total of 9292 doses of Penta1 during the course of 1 year. On the basis of the number of caregivers that needed to be screened (2907) and the number of doses the 3 health facilities provided in a year (9292), we estimated that 16 weeks would be necessary for enrollment. After the first 2 months of study recruitment (February-March 2016), enrollment was found to be lower than expected, so a fourth health facility was added as a study site.

### Ancillary Research Objectives

In addition to the RCT study design to address the principal research objectives, we also conducted focus group discussions (FGDs) to more thoroughly assess caregiver acceptability of a personalized, automated caregiver text message reminder intervention. At the end of the study, study personnel conducted 8 FGDs with caregivers and spouses who were originally randomized into the intervention group from one of the select health facilities. A total of 4 types of FGDs were conducted:

Female caregivers who received messages on their personal phones and whose children were up to date with vaccinationsFemale caregivers who received messages on their personal phones and whose children were not up to date with vaccinationsFemale caregivers’ spouses who received messages on their personal phones and whose children were up to date with vaccinationsFemale caregivers’ spouses who received messages on their personal phones and whose children were not up to date with vaccinations

The FGDs were audiorecorded, and 2 research assistants translated and transcribed (1 step) discussions into English. Thematic content analysis will serve as a strategic analytical approach. Codes will be identified and then refined through additional reviews of the data. The main themes will be identified, reviewed, further refined, categorized, and subcategorized; matrix analysis will be used to organize themes and assess patterns. Data will be analyzed using word processors, spreadsheets, and qualitative data analysis software.

In addition, we will conduct an economic analysis that will focus on evaluating the incremental costs and cost-effectiveness of the personalized, automated caregiver text message reminder intervention compared with standard practice. Costs will be evaluated from the provider (MOH) perspective and will include the start-up costs of developing the system and operational costs of delivering the text messages (including costs related to data charges for message deployment, system maintenance, and troubleshooting). For the calculation of incremental cost-effectiveness ratio (ICER), coverage data from the questionnaire will be an important determinant in evaluating the value for money in adopting the caregiver text message reminder strategy. Effectiveness will be measured by the cost per additional fully immunized child at 12 months of age in the intervention arm. Furthermore, we will estimate the costs of scaling up the proposed intervention by the MOH to cover the entire country using data on the expected catchment areas for health facilities in Uganda to determine the total cost of a nationwide system rollout. Sensitivity analysis will be conducted to determine how sensitive the ICER is to varying effectiveness and system costs.

